#### 3.2.2. Body Composition, Bone Mineral Density, and Bone Architecture

Dual energy x-ray absorptiometry (DXA, Hologic Horizon A, Waltham, MA, USA) will be used to assess bone mineral density (whole body, lumbar spine, and hip) and body composition (regional and whole body fat and fat-free mass), allowing the assessment of the metabolic status of bone and identification of the risk level for future fractures [59]. Bone architecture will be assessed by peripheral quantitative computed tomography (pQCT; XCT-3000, Stratec Medizintechnik GmbH, Pforzheim, Germany), a non-invasive low radiation method for assessing three-dimensional bone microarchitecture and volumetric bone mineral density in cortical and trabecular compartments of the femur and distal radius [60]. Scans of the skeletally non-dominant leg and forearm will be performed with skeletal dominance determined from functional dominance. Femur and radial length will be measured to the nearest millimeter with an anthropometric ruler. Femur length will be measured as the distance from the apex of the lateral epicondyle to the inguinal crease. Radial length will be measured as the distance from the tip of the radial head to the tip of the radial styloid process. Two image slices of the femur (4% and 33% of femur length proximal to the distal endplate) and two image slices of the radius (4% and 66% of radial length proximal to the distal endplate) will be obtained. The scan parameters will be voxel size, slice thickness, and scan speed of 0.5 mm, 2.3 mm, and 20 mm/s, respectively. A planar scout view over the joint line will be acquired in order to place the anatomic reference line. Analyses will be conducted using host software (Version 6.20, Stratec Medizintechnik GmbH, Pforzheim, Germany).

#### 3.2.3. Anthropometry

Body mass index (BMI) and waist–hip ratio will be measured according to the international standards for anthropometric assessment [61]. Body mass and stature will be measured using an electronic, calibrated scale (A & D Mercury, Pty Ltd., Thebarton, Australia) and standard stadiometer (Seca, Birmingham, UK), respectively. These measures will be used to calculate BMI and to track changes in body mass. Waist circumference will be measured using an anthropometric steel tape measure (Lufkin W606M retractable steel tape; Cooper Tools) at the narrowest point between the lowest costal border and iliac crest, while hip circumference will be measured at the level of greatest posterior gluteal protuberance. These measures will be used to calculate the waist–hip ratio and to track changes in the waist circumference.

#### 3.2.4. Neuromuscular Strength and Balance

##### Grip Strength

Grip strength will be used as an indicator of upper extremity body strength and assessed for the dominant and non-dominant hands using a spring-resistance dynamometer (TTM Advanced Analogue Hand Grip Dynamometer, Tokyo, Japan), as previously described [62]. Grip strength is an independent predictor of mortality in older adults and can potentially identify patients, including those with a high level of function, who are at risk of deteriorating health [63].

##### Leg Neuromuscular Power

The 30 s sit-to-stand (30STS) test is used as a measure of lower limb neuromuscular power, as it involves activation of multiple muscles of the lower limb, most notably the gluteal and knee extensor (quadriceps femoris) muscles [64]. It is also able to assess the fatigue effect caused by the number of sit-to-stand repetitions. In a population of well-functioning 70- to 79-year-olds, those with sit-to-stand times in the high risk group were more likely to experience adverse health-related events, such as persistent (severe) lower extremity limitation, death, and hospitalization (hazard ratio = 1.59, 95% CI: 1.41, 1.78 (*p* < 0.001)) [65]. Participants will be required to stand up and sit down on a standard armless chair as quickly as safely possible for 30 s. Participants will fold their arms across their chest and be instructed to stand up completely and make firm contact when sitting. Timing will begin on the command “go” and cease after 30 s. Only one test trial will be performed to minimize fatigue.

##### Isometric Mid-Thigh Pull

Given the high proportion of bone lesions in people with MM, the isometric mid-thigh pull will be used as a measure of body strength. Strength measured via the isometric mid-thigh pull has been shown to correlate with overall body strength [66] and has been used in cancer populations to determine responses to concurrent resistance training and high intensity interval training [67]. It requires little familiarization and can be implemented across a range of populations, including older adults. All measures will be performed using a custom isometric testing device that includes a step-wise adjustable bar and a portable force plate for measuring ground reaction forces (Kistler, Ostfildern, Germany) [68], with sampling at 1000 Hz from the vertical axis using native software (Kistler Bioware 5.3.2.9, Ostfilferm, Germany). The peak or highest force output will be recorded and used as a measure to indicate maximal lower limb muscle strength.

##### Y-Balance Test

The Y-Balance Test (YBT) is a simple, reliable tool to measure dynamic balance. It has a high level of test–retest reliability and has been shown to have strong relationships with knee flexor and hip abductor strength [69]. The test measures the participant’s strength, stability, and balance on one leg whilst simultaneously reaching as far as possible in three separate directions (anterior, posterolateral, and posteromedial) with the other leg. The YBT composite score is calculated by summing the three reach directions and normalizing the results to the lower limb length [70]. The ability to balance on each leg in a static stance will be assessed prior to completion of the YBT to indicate any safety concerns. A duration of >30 s will be classified as successful test completion.

#### 3.2.5. Pain and Bone Pain

Pain will be assessed via the Brief Pain Inventory (BPI), previously known as the Brief Pain Questionnaire, a self-administered questionnaire that was originally designed to assess cancer pain. Test–retest reliability has been assessed for malignant pain and shows good reliability for pain intensity (Cronbach’s α = 0.8) and pain interference (Cronbach’s α = 0.8) [71]. Internal consistency is high for the severity scale (0.81 < α < 0.89) [72] and interference scale (0.88 < α < 0.95) [73].

Bone pain will be assessed using the Functional Assessment of Cancer Therapy Bone Pain Subscale Questionnaire (FACT-BP), which has been validated for use in cancer populations [74]. The scale has been shown to be a robust and concise tool for assessing cancer-related bone pain, in addition to the impact of that pain upon functioning and quality of life. The internal consistency reliability coefficients for the questionnaire exceed acceptable standards (Cronbach’s α = 0.93–0.96), with evidence of construct validity. Known-group validity was supported by score shifts in the anticipated direction (Cohen’s d effect size = 0.36).

#### 3.2.6. Cancer-Related Fatigue (FACIT-F)

Cancer-related fatigue will be assessed using the Functional Assessment of Chronic Illness Therapy Fatigue Subscale Questionnaire (FACIT-F). The FACIT-F has been previously reported to have high reproducibility and validity (Cronbach’s α = 0.95–0.96), with good divergent validity to discriminate between levels of disease severity and functional status [75] and hemoglobin (used as a measure of fatigue) [76]. The FACIT-F has 43 items in total and includes five subscales: physical, functional, social/family, emotional well-being, and a fatigue-specific domain.

#### 3.2.7. Functional Disability (Oswestry Low Back Pain Disability Questionnaire)

The Oswestry Low Back Pain Disability Questionnaire (OLBPDQ) will be used to measure permanent functional disability. The test is considered the “gold standard” of low back functional outcome tools. It is a unidimensional scale with overall excellent construct validity, good internal consistency (Cronbach’s α = 0.85), and the ability to discriminate the severity of functional disability [77].

#### 3.2.8. Myeloma-Specific Patient Reported Outcomes (MyPOS and FACT-MM)

Myeloma-specific patient reported outcomes will be assessed using the Myeloma Patient Outcome Scale (MyPOS) and the Functional Assessment of Cancer Therapy Multiple Myeloma subscale Questionnaire (FACT-MM). The MyPOS is a 30-item, myeloma-specific version of the Palliative Care Outcome Scale. It was developed through a qualitative investigation of the issues most important to the HRQoL of people with MM and is a valid and reliable tool for use in the routine clinical care of myeloma patients (Cronbach’s α = 0.89) [78]. Factor analysis confirmed three subscales; (i) symptoms and function (14 items covering physical symptoms and functional impairments); (ii) emotional response (8 items describing the emotional impact of the disease); and (iii) healthcare support (5 items on information needs and satisfaction with healthcare). Higher scores represent worse HRQoL.

The FACT-MM [79] has 14 items which are a disease-specific, patient-reported outcomes measure for the assessment of HRQoL among people with MM. Participants will indicate how true the scale items are for them on a scale from 0 (not at all) to 4 (very much).

#### 3.2.9. Falls Self-Efficacy (Falls Efficacy Scale—International (FES-I))

The Falls Efficacy Scale—International assesses the level of concern about falls during 16 activities of daily living, ranging from basic to more demanding activities, including social activities, which may contribute to quality of life. It was originally developed to assess concern about falls in older people [80]. The FES-I has excellent reliability and validity with regard to external physiological and neuropsychological measures [80,81]. The level of concern for each item is scored on a 4-point scale (1 not at all, 2 somewhat, 3 quite a lot, 4 very), with the total score ranging from 16 to 64.

#### 3.2.10. Blood Biomarkers

A qualified and experienced phlebotomist will complete all blood collection procedures. Blood (24 mL) will be sampled from an antecubital vein using a 23-gauge needle and collected into 4 × 6 mL plastic vacutainers (BD), uncoated for serum collection (1 × 6 mL) and coated with anticoagulant agent K_2_EDTA (2 × 6 mL) and lithium heparin (1 × 6 mL) for plasma. Plasma samples will be immediately stored on ice, whilst serum will be allowed to clot at room temperature for 60 min before centrifugation at 3000 rpm for 10 min (approximately 900× *g*) at −4 °C. Plasma and serum samples will be pipetted into 0.3 mL aliquots, frozen at −80 °C, and stored for subsequent analyses.

##### Adipokines

Bone marrow adipose tissue (BMAT) interrelates with bone marrow cells and other immune cells, and several studies have identified BMAT as a key driver in MM progression [82,83,84,85]. BM adipocytes isolated from MM subjects have been shown to increase myeloma growth in vitro and may preserve cells from chemotherapy-induced apoptosis [82]. They may have a role in MM progression, bone homing, chemoresistance, and relapse, due to local endocrine, paracrine, or metabolic factors [83,84,85]. Preclinical results indicate that modifying adipose tissue and BMAT could be a successful MM therapy [86]. Exercise can alter BMAT [87] and can alter the secretion by adipocytes of numerous adipokines [88]. The levels of plasma total and high molecular weight adiponectin will be measured by enzyme-linked immunosorbent assay.

##### Bone Health

Markers of bone resorption (C-terminal (CTX) telopeptide of type 1 collagen) and formation (alkaline phosphatase (total and bone specific), procollagen type 1 N-terminal propeptide (P1NP)) will be measured by enzyme-linked immunosorbent assay.

##### Immune Function

Specific markers of immune function will be assessed using flow cytometry. As a general marker of inflammation, high-sensitivity C-reactive protein will be measured by immunoturbidimetric assay. Using multiplexed bead-based immunoassay, an inflammatory cytokine panel of 16 markers (IL-1beta, IL-2, IL-4, IL-5, IL-6, IL-8, IL-10, IL-13, TNF-alpha, G-CSF, MCP-1, GM-CSF, IFN-alpha, IFN-gamma, IL-17A, IL-12p40) will be analyzed.

##### Metabolomic and Lipidomic Analyses

Untargeted metabolomic and targeted plasma lipidomic profiles will be determined using liquid chromatography-coupled tandem mass spectroscopy analysis [89,90]. In addition, extracellular vesicles will be isolated from plasma for untargeted proteome and targeted lipidome analyzed by liquid chromatography-coupled tandem mass spectroscopy [91]. Since changes in the serum metabolomic profile and extracellular vesicles have been observed in MM patients after remission [92] and associated with progression [93], the disease and treatment status of patients will be noted before interpretation.

#### 3.2.11. Self-Reported and Objective Physical Activity

The Godin Leisure Time Physical Activity Questionnaire (LTPAQ) will be used to track the self-reported physical activity behaviors [94]. The Godin LTPAQ requires participants to recall during a typical seven day week the frequency and duration of leisure-time physical activity completed at three separate intensities: mild, moderate, and vigorous intensity. The Godin LTPAQ has been shown to have a modest correlation compared with accelerometry-derived measures of physical activity of at least moderate intensity in cancer survivors (r = 0.46) [95] and demonstrates high test–retest reliability (r = 0.75) [96].

Objective physical activity will be measured using the Actigraph wGT3X-BT, a valid, inclinometer/accelerometer that measures time spent sitting, standing, and stepping (overall and at a light or moderate-to-vigorous physical activity intensity) [97,98,99]. Participants will be asked to wear the device on an elastic waist belt aligned with the right anterior axillary line during waking hours for seven days after each testing session. Participants will be asked to complete a wear-time log and activity diary during the monitoring period, recording wake and sleep times, and, if the monitor was removed, the duration and reason (showering, bathing, swimming, sleeping, or engaging in contact sport). Accelerometers will be initialized with 30 s epochs and a 30 Hz sampling frequency. A valid day will be defined as a minimum wear-time of 10 waking hours, with non-wear-time defined as 60 min or more of consecutive activity counts of zero. For activity data to be included, participants must satisfy a minimum wear-time criterion of at least four of the seven days, with at least one of the days being a weekend day [100]. ActiGraph wGT3X-BT data will be processed using R-Package GGIR [101] to calculate time in sedentary (<30 mg), light (30–99 mg), moderate (100–399 mg), and vigorous (400+ mg) PA using the widely recognized thresholds proposed by Hildebrand et al. [102]. Additionally, sedentary behavior and moderate-to-vigorous PA will be estimated in bouts of 30 min and 1–5, 5–10, and >10 min, respectively.

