## Abstract

People with multiple myeloma (MM) are second only to people with lung cancer for the poorest reported health-related quality of life (HRQoL) of all cancer types. Whether exercise can improve HRQoL in MM, where bone pain and lesions are common, requires investigation. This trial aims to evaluate the efficacy of an exercise intervention compared with control on HRQoL in people with MM. Following baseline testing, people with MM (*n* = 60) will be randomized to an exercise (EX) or waitlist control (WT) group. EX will complete 12-weeks of supervised (24 sessions) and unsupervised (12 sessions) individualized, modular multimodal exercise training. From weeks 12–52, EX continue unsupervised training thrice weekly, with one optional supervised group-based session weekly from weeks 12–24. The WT will be asked to maintain their current activity levels for the first 12-weeks, before completing the same protocol as EX for the following 52 weeks. Primary (patient-reported HRQoL) and secondary (bone health and pain, fatigue, cardiorespiratory fitness, muscle strength, body composition, disease response, and blood biomarkers) outcomes will be assessed at baseline, 12-, 24- and 52-weeks. Adverse events, attendance, and adherence will be recorded and cost-effectiveness analysis performed. The findings will inform whether exercise should be included as part of standard myeloma care to improve the health of this unique population.

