### 2.4. Randomization

Following completion of the baseline testing session, participants will be stratified by disease stage (active treatment, transplant eligible; active treatment, transplant non-eligible; non-active; relapsed) before being randomly assigned (1:1 allocation ratio) to waitlist control (WT) or exercise intervention (EX) group. A research officer independent of the study will perform the randomization using a computerized random number generator. To ensure allocation concealment, a block size of four will be used. Randomization history will be kept secure by the independent research officer in an electronic password-protected file. The allocation result will be communicated in confidence by the independent research officer to the trial’s accredited exercise physiologist (AEP) within 48 h after completing the baseline testing session. The principal investigator will conduct all testing sessions and analyses and be blinded to group allocation. Un-blinding will not be permissible under any circumstances. Due to the nature of the study, neither the AEPs prescribing the training nor participants can be blinded to the randomization assignment.

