### 2.5. Exercise Intervention

Participants will complete the modular multi-modal resistance, aerobic, and impact loading exercise program under the supervision of the trial AEP on two days per week, in addition to one home-based session. Supervised exercise sessions will be offered at multiple locations across southeast Queensland, Australia: North Lakes Health Precinct, Greenslopes Private Hospital, Princess Alexandra Hospital, Royal Brisbane and Women’s Hospitals Hospital, and The University of Queensland. A familiarization session with the trial AEP will be completed in the week prior to commencement to explain the exercise program and guide participants through several exercises that are more technically challenging. The 60 min training session will follow the procedure as described in Figure 2. The exercise intervention is designed to provide an optimal stimulus to the cardiorespiratory, skeletal, and neuromuscular systems while maximizing compliance and retention. The program adheres to the American College of Sports Medicine (ACSM) Guidelines for Exercise and Cancer for improving HRQoL [8]. The exercise prescription will be individualized by the trial AEP based on the participants’ goals, exercise history and preferences, baseline testing results, and health status, including location/extent of bone metastases. All participants will be asked to maintain customary physical activity and dietary patterns over the intervention period (apart from the programmed exercise).

Prior to each supervised session, the trial AEP will measure the participants’ heart rate (HR) and blood pressure to identify potential contraindications to commencing exercise, as outlined by the ACSM [40]. Each session will commence with a 5 min warm-up comprising low-impact aerobic activities, such as stationary cycling, at a progressive very light/light intensity (rating of perceived exertion (RPE) of 9–10 on the 6–20 Borg Scale), and conclude with a 5 min cool-down period of stretching activities.

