## 5. Statistical Considerations and Data Analyses

A priori power calculations determined that a sample of 44 participants (*n* = 22 per group) will be needed to detect a mean difference of 6.7 points [51] between groups on the EORTC QLQ-C30 MY20 after the 3-month supervised exercise phase, with 80% power and 5% alpha. To account for an anticipated dropout rate of 25%, 60 participants will be recruited to the study. A difference of 6.7 on the physical function subscale of the EORTC QLQ-C30 MY20 questionnaire, determined by receiver operating characteristic curve analysis, corresponds to the minimum clinically meaningful change considered important by people with MM [51].

Data will be analyzed using the Stata statistical software package (version 15.0, StataCorp, College Station, TX, USA). Data entry will be performed in duplicate, and accuracy will be assessed with automatic cross-checking procedures. Range checks for data values will be performed to promote data quality. Data will be assessed for normality using the Shapiro–Wilk test. Subsequent analyses will include standard descriptive statistics, *t* tests, correlation, regression, and one-way repeated measures ANOVA or the comparable non-parametric test as necessary to examine differences among timepoints. Each model will include covariates, as appropriate, and will be adjusted using the baseline value as a fixed continuous covariate. For accelerometer data, means and 95% confidence intervals will be calculated and repeated measures accounted for across multiple days within participants. Quality of life questionnaire items will be analyzed using random effects mixed modelling with Fisher’s least significant difference tests for post hoc analyses to compare mean changes in outcomes between groups at each assessment period, with time and group as the fixed factors. A time × group interaction term will be used to formally test for differences between groups (alpha = 0.05).

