There are several limitations of the proposed study that warrant discussion. Our target population will be limited to those who are able to attend frequent testing and training visits and who are able to obtain an approval to participate from their treating physician. Arguably, those who are frailer, with limited mobility, and who may elicit a greater response from the intervention, will not be included in the study. Whilst the heterogeneous group of people with MM will demonstrate the ability of exercise to elicit improvements across the MM continuum, the study is not powered to conclude its effects within specific disease stages. Finally, the waitlist control group may increase their physical activity, despite being asked to maintain their activity levels for the first 12 weeks, reducing our ability to observe effects of the intervention.

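### Accelerometer wear follows each test, so most of the 'baseline' week can fall after allocation and the 3-month week falls after the randomised contrast has closed

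*Protocol article*

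**What the plan says.** Section 3.2.11 fixes the wear period: the device is worn "during waking hours for seven days after each testing session". Table 1 schedules accelerometry at baseline, 3, 6 and 12 months. A record counts if at least four of the seven days are valid, one of them a weekend day.

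Section 2.4 fixes allocation: "Following completion of the baseline testing session, participants will be stratified by disease stage" and are then assigned. The result goes to the trial's exercise physiologist "within 48 h after completing the baseline testing session", and "neither the AEPs prescribing the training nor participants can be blinded to the randomization assignment". Section 2.5 adds: "A familiarization session with the trial AEP will be completed in the week prior to commencement".

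On the close of the comparison, section 2.1 places the EX test at the end of the supervised phase. Footnote a to Table 1 repeats the baseline battery in WT after three months of usual care. The Abstract asks WT to "maintain their current activity levels for the first 12-weeks, before completing the same protocol as EX for the following 52 weeks". The stepped-down supervision part of section 2.5 moves EX to home-based sessions with an optional weekly class after week 12.

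Section 5 says that each model "will be adjusted using the baseline value as a fixed continuous covariate".

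**The concern.** A baseline covariate should be measured before randomisation, so that treatment cannot have influenced it. An outcome used to compare EX with WT should be measured while the two groups are still being treated differently. The wear rule does not secure either condition for accelerometry.

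If knowledge of the allocation, or early contact with the exercise physiologist, changes activity in the first wear week, adjusting for that week removes part of the effect being estimated. If the groups converge once the 12-week period closes, the 3-month wear week understates the difference that existed during it. In their expected direction, both pull the comparison towards no difference.

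The Discussion (section 7) also concedes that "the waitlist control group may increase their physical activity, despite being asked to maintain their activity levels". Accelerometry is the objective activity measure that could show this. As scheduled, it records nothing between the first week and the 12-week test.

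**Working it through.** The article states no figure to reproduce. The check sets the dates side by side and then illustrates how a bias would arise.

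**Baseline wear against allocation**

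- Wear: days 1 to 7 after the baseline session (section 3.2.11).
- Latest notice to the exercise physiologist: 48 h, or 2 days, after that session (section 2.4).
- Days beyond that limit: 7 − 2 = 5 of 7, or 71%. Earlier notice leaves more days after it.
- Four valid days suffice, so a participant's entire valid record can come from those days, provided they include a weekend day.
- No section gives a wear period before randomisation, or holds back the notice, the familiarisation session or the first training session until wear ends.

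**Three-month wear against the end of the contrast**

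- Wear: days 1 to 7 after the 3-month test, so 0 of 7 days precede the test that closes the comparison.
- EX in that week: due to step down from two supervised sessions and one home session a week to home-based sessions.
- WT in that week: its 12-week instruction has ended and the same programme comes next. The start date is not fixed.

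**How a bias would arise**

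Let D be the true activity contrast during the intervention, f the share of D already present in the 'baseline' week, g the share of D remaining in the week after the 12-week test, and ρ the slope of follow-up on baseline. Randomisation makes the true baselines equal on average, so

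expected adjusted contrast = g·D − ρ·f·D = (g − ρf)·D.

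None of f, g or ρ is in the article. The values below are assumptions that show a range.

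| f | g | ρ = 0.5 | ρ = 0.7 |
|---|---|---|---|
| 0 | 1 | 1.00 | 1.00 |
| 0.10 | 0.75 | 0.75 − 0.05 = 0.70 | 0.75 − 0.07 = 0.68 |
| 0.25 | 0.50 | 0.50 − 0.125 = 0.375 | 0.50 − 0.175 = 0.325 |

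The first row has no bias: behaviour does not shift in the first week and the full contrast persists after the test. The article secures neither condition. Analysing change from baseline would not help, because ρ is then replaced by 1 and the shift f is subtracted in full.

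**The case against.** The strongest reply is that the dates make bias possible without showing that it occurs, and that its size may be small. Much of this stands.

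- The 48 h limit concerns notice to the exercise physiologist. The article does not say when participants learn their arm.
- All participants are asked to keep to customary activity apart from the programme, and familiarisation need not fall in the wear week. A reader might infer that treatment has already moved the baseline; the documents show only that it could have.
- EX is still prescribed three sessions a week after week 12. A reader might infer that EX loses its supervised time (2 × 60 = 120 min a week) while WT gains up to a full programme (3 × 60 = 180 min), so that a true difference is cancelled or reversed. This does not follow: EX loses supervision while its prescription continues, and no WT start date is given. In the formula above, reversal needs ρf to exceed g, meaning almost no contrast remains, and nothing in the article supports that. Nor does it support any bias expressed in minutes per week.
- No section assigns accelerometry the task of checking waitlist activity. The Godin questionnaire is collected at the same visits and asks about a typical week. It is self-reported by unblinded participants, however, and section 3.2.11 itself reports only a modest correlation with accelerometry (r = 0.46).
- Wear before a test could include the 24 h activity restriction in section 3. That restriction applies to both groups at every visit, and wear can end before it starts.

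What remains is the sequence itself, which the article fixes and no other section corrects.

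**Conclusion.** The point holds as a timing fault. Followed as written, most of the accelerometer 'baseline' week can fall after allocation in participants who are not blinded, and the 3-month wear week lies wholly after the test that closes the 12-week contrast. The comparison of device-measured activity between EX and WT can be biased, probably towards no difference.

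The size is unknown. It depends on when participants learn their arm, on the gap between each test and the next training session, and on how activity changes in those weeks, none of which the article fixes. It could be negligible if WT starts only after the wear week and EX keeps up its activity. The direction assumes that EX is, if anything, more active in the first wear week and that the groups converge after week 12.

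The scope is one secondary outcome. The primary quality-of-life comparison is not affected, nor is the Godin questionnaire. The change is worth making because the flaw is built into the schedule and cheap to remove.

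**What to change.** Move the wear weeks; no new measurement is needed.

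- **Baseline:** complete the seven days of wear before randomisation. Alternatively, keep wear after the test but withhold the allocation notice and familiarisation until it is complete.
- **12 weeks:** complete wear within the last week of the randomised period, before EX supervision steps down and before any WT familiarisation or training.
- **Both:** where wear precedes a test, end it before the 24 h activity restriction begins.

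State in section 3.2.11 how each wear week sits relative to allocation and to the start of training, so that the baseline covariate in section 5 is a pre-randomisation value.

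The cost is that the device must be issued about a week earlier, or that randomisation or the WT start is delayed by up to seven days. Participants already complete a 3-day diet diary before the baseline session, so some contact before the visit exists.
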